
**Figure 2 fig2:**
[figure not shown]
Screenshots of the privacy dashboard, where user can manage permissions and find information about data sharing.

**Figure 3 fig3:**
[figure not shown]
e-VITA dashboard access page that is shown when opening the app **(A)** landing page, **(B)** login page, and **(C)** sign up page.

**Figure 4 fig4:**
[figure not shown]
e-VITA dashboard settings control—**(A)** language settings, **(B)** settings page, and **(C)** dashboard lateral menu to access settings.

**Figure 5 fig5:**
[figure not shown]
e-VITA dashboard homepage where all the apps and services are shown and accessible.

Figure 6 shows some screenshots of the Social Platform.

**Figure 6 fig6:**
[figure not shown]
Screenshots of social platform—**(A)** thematic groups of interests to which the user can subscribe and **(B)** view of the members of one group.

### Use case configurator (UCC)

The Use Cases Configurator (UCC) stands as an independent software component within the e-VITA platform, which is tasked with translating user needs, environmental requirements, and configuration settings into technical specifications for the sensing and coaching system. This configurator prioritizes the creation of a smart living environment that balances cost-effectiveness and sensor efficiency, ensuring accurate measurements while identifying optimal devices for virtual coaching. The overarching goal is to deliver a service tailored to users’ needs and preferences. The UCC features a graphical interface, offering insights of end-users into the composition of the e-VITA platform based on their selected information, preferences, and goals. Inputs for the configurator include the needs and requirements of older adults, encompassing details about the living environment (house architecture, rooms, etc.), living situation (single or multiple residents), sensor acceptance (wearable or stationary sensors), privacy settings, and personal information (gender, age, and religion).

### Emotion detection system (EDS) module

The e-VITA Emotion Detection System (EDS) module will serve as one of the basic foundations for an empathic coaching system. That is, by accurately detecting the end-users’ emotional state, the EDS enables subsequent, high-level components to flexibly adjust their functioning and end-user interaction, in order to achieve a higher level of acceptance, usability, and well-being. The EDS layer imports audio samples from the current speech of the user (pseudonymized) during the interaction with the coaching devices via speech. Then, it pre-processes these data and decomposes the audio signal into its statistical sub-components (anonymized, no reverse-engineering possible). Based on this, a classification layer detects the currently most prominent emotion from a fixed set of basic emotions. Another approach will be to add a sentiment analysis to the EDS. This means, that in addition to the acoustic features of the audio data coming from the participant, information is extracted that is related to the participant’s sentiment or opinion, based on Natural Language Processing (NLP). For this, the audio data will be transcribed to a text, which will be then analyzed based on keywords, that represent a basic emotion. This information will be then added to the results of the acoustic analysis, leading to a final model with labels of basic emotions such as anger, disgust, fear, joy, neutral, and sadness. As a result, components, directly modeling the interaction with the end-user, for instance, dialog management, can then be augmented to fit the user’s emotional state.

### Outcome measures

All outcomes will be measured following a standardized operating procedure. The primary endpoint of the study is constituted by the improvement in the quality of life after the use of the e-VITA system, to be measured through the EQ-5D-5L, after 6 months of training.

The secondary endpoints encompass: (1) adherence to the coaching intervention, measured by the frequency of technological device usage, and collected through semi-structured interviews and technical data; (2) usability and the user experience of the overall system assessed using the System Usability Scale (SUS) (62) at both the midpoint and the conclusion of the experiments, along with the User Experience Questionnaire [UEQ (63) and UEQ+ (64)] in the middle and at the end of the experiments; (3) improvement in eHealth literacy, to be addressed through the eHealth Literacy Scale (eHEALS) (65), social connectedness through the UCLA Loneliness scale (UCLA) (66), nutritional state through the short version of Food Frequency Questionnaire (FFQ) (67) to estimate the frequency of daily food intake over a period, cognitive status, through Montreal Cognitive Assessment (MoCA) (39), psychological mood through the Geriatric Depression Scale (GDS) (40), functional status through Short Physical Performce Battery (SPPB) (41), participation to leisure activities through an *ad-hoc* checklist; meets the participant’s objectives through ADTPA-5 (scale B and E adapted) (68). A semi-structured interview will be used to complement the information collected by questionnaires, focusing on acceptability, attitude, usability, and cost–benefit analysis; other questionnaires will be used to better understand our participants’ sociodemographics questionnaire, Clinical Frailty Scale (CFS) (38), Big Five Inventory – 10 (BFI-10) (69), and Affinity for Technology Interaction (ATI) (70).

Table 3 presents a concise overview of all collected data and their respective collection time points.

**Table 3 tab3:** Schedule of assessment and outcome measures.

Dimension	Scale	R	T0	T1	T2
Clinical frailty scale	CFS	X			
Cognitive status	MoCA	X			X
Psychological status	GDS	X			X
Physical capacity	SPPB	X			X
Overall health status	Clinical anamnesis	X			
General information	Socio-demographics questionnaire	X			
Quality of life	EQ-5D-5L		X		X
Goals and expectation	ATDPA-5 (Scale B and E)		X		X (Scale B)
eHealth literacy	eHEALS		X		X
Social connectedness	UCLA		X	X	X
Personality	Big Five Inventory – 10 items		X		
Nutrition	Short FFQ		X		X
Adherence	Collected through the system and interview			X	X
Leisure activities	Physical and leisure activity checklist		X	X	X
Usability	SUS			X	X
User experience	UEQ, UEQ+			X	X
Attitude, usability, acceptability and cost–benefit analysis	Semi-structured interview				X
Affinity for technology interaction	ATI		X		

R, recruitment; T0, first evaluation; T1, intermediate evaluation; T2, final evaluation; CFS, Clinical Frailty Scale; MoCA, Montreal Cognitive Assessment; GDS, Geriatric Depression Scale; SPPB, Short Physical Performance Battery; ATDPA, Assistive Technology Device Predisposition Assessment; FFQ, Food frequency questionnaires; SUS, System Usability Scale; UEQ, User Experience Questionnaire; ATI, Affinity for Technology Interaction.

The scales which will be used during the evaluations are described below.

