
Through a personalized approach, the virtual coaching system can enable people to live a healthy lifestyle, identifying personal needs and goals and providing appropriate risk predictions and individualized recommendations (23, 24). These devices cover a variety of domains and audiences (25). There are a multitude of virtual coaches and apps for the promotion of nutrition (26), physical activity (27), mood, sleep (28), and even more clinical applications, such as rehabilitation (29) or monitoring of cardiovascular pathologies (30).

There are virtual coaches for adults, children with autistic disorders, and older adults. These tools have attracted interest from healthcare organizations and consumers for promoting health, wellness, physical activity, and lifestyle improvement (31). The use of these virtual coaches and apps has great potential to help older adults improve their quality of life by addressing age-related issues and the physical and social implications of aging (32). Moreover, embracing these proactive measures with the assistance of a virtual coach empowers older adults to maintain independence and comfortable living in their homes for an extended period (33). This reduces the need for constant monitoring by health professionals, limits the costs that would otherwise be incurred (32), and helps mitigate the wider impact of demographic aging on healthcare (4).

However, the technologies developed for healthy and active aging have some limitations. Indeed, they are mainly used for short period of time and are poorly integrated into the daily lives of older adults, thus limiting their benefits (6). Moreover, interactions with these technologies are not ideal since they do not lead to realistic and satisfying social interactions due to technologies that are not yet advanced enough (34). It is therefore necessary to design and evaluate new products that consider the needs and preferences of seniors and their relatives for a sustainable and optimal use of these devices (35). The aim is to enable seniors to live independently in their own homes for as long as possible, preventing social isolation and encouraging active participation in social and group activities.

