### Risk–benefit analysis

During the use of robotic platforms or, in wider terms of technological applications, a general difficulty in distinguishing between the artificial world and reality may occur. Especially, in the case of vulnerable older adults, the interaction may generate a general feeling of attachment and dependency. To avoid this, e-VITA has been designed to not look like a human but to preserve artificial aesthetics, as suggested by the guidelines. In addition, during the first contact with the participants but also during all the interventions, researchers will be in contact with the users, continuously stimulating awareness about the technological applications and monitoring the appropriateness of the use of the solution in terms of autonomy of the users, specific needs, and personal preferences. In particular, following the recommendations provided by Comitato nazionale di bioetica (Cnb) of the Ministry of Health (71) on robotics and roboethics, the exit strategy of e-VITA will aim to:

promote adequate experimentation of robotics in the field assistance in order to ensure conditions for the physical and psychological integrity of the user, explaining the risks and benefits, which was highlighted also in the informed consent;ensure both equitable access to robotic and general technologies and the use of robots to assist and not to replace humans, in order to avoid delegating the irreplaceable human task of care and assistance to the machine;the need that the introduction of robotics in medicine entails always the real consideration of the benefits, of the complexity of the change complete with the structure of the services and the economic burden that this entails.

There is a risk that the older adults may wish to stop interacting with the technological devices (for example, because they do not like the NAO robot). In this case, the experiment will be immediately stopped and terminated.

The presence and use of technological devices (virtual coaches and sensors) in participants’ homes can be a source of discomfort. Therefore, pre-studies with end-users (older adults) and stakeholders (informal carers, health professionals, family, NGOs etc.) have been carried out in order to propose virtual coaches that meet the needs of older adults. In addition, safety procedures were also designed to limit the risks as much as possible.

To protect the safety of participants:

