#### Data collected by the technological devices

One of the uses of the data collected from the sensors is to infer the activity of the user and know his or her location so that the voice coach carries out personalized dialogs adapted to the contexts of the user. The environmental data will be used to identify dangerous situations and difficulties and inform the user by giving him the right recommendation to remedy this situation. The aggregation of activity data from several testing centers will serve to motivate users and strengthen their adherence to the experiment. The analysis of user activity data and their interactions at well-defined milestones in the experiment will make it possible to detect system failures as early as possible, in order to prevent the user from dropping out.

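### Participants who stop because they reject the coach have no scheduled SUS or UEQ rating afterwards, so usability is likely to be overstated; adherence is at risk only if stoppers, or their time after stopping, go uncounted

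*Protocol article*

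**What the plan says.** The first secondary endpoint (Outcome measures) is "adherence to the coaching intervention, measured by the frequency of technological device usage, and collected through semi-structured interviews and technical data". Table 3 marks adherence at T1 and T2, with the source given as "Collected through the system and interview". The second secondary endpoint is usability and user experience. It uses the "System Usability Scale (SUS) (62) at both the midpoint and the conclusion of the experiments", with UEQ and UEQ+ at the same two points. The semi-structured interview on attitude, usability and acceptability is marked at T2 only. Table 3 is presented as the overview of everything collected and when, and it has no column for early termination.

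The Risk–benefit analysis section foresees participants who give up the devices: "There is a risk that the older adults may wish to stop interacting with the technological devices". Its example is a person who does not like the NAO robot. The consequence is: "In this case, the experiment will be immediately stopped and terminated". The text does not say whether such a person is still assessed at T1 or T2.

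Two further statements concern use data. The section on data collected by the technological devices plans "The analysis of user activity data and their interactions at well-defined milestones in the experiment", partly to keep users from dropping out. The Data management section keeps the number of interactions logged with each participant, describes that count as anonymous, and discards the robot's other recordings.

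**The concern.** The protocol's own example ties stopping to dislike of the coach, and that is what SUS, UEQ and UEQ+ measure. Missing usability scores are therefore probably related to the score that would have been given. This is a data-collection matter: if a rating was never taken, no later analysis plan can recover it.

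The stakes lie in the description of e-VITA itself. In its Background, the article says of existing technologies for healthy ageing that "they are mainly used for short period of time and are poorly integrated into the daily lives of older adults". That is one of the limitations that motivate the project. A usability summary without the people who abandoned the system would be weakest on that question.

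**Working it through.** **Schedule and stopping statement side by side**

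| Participant | SUS, UEQ/UEQ+ at T1 | SUS, UEQ/UEQ+ at T2 | Acceptability interview (T2) | System log |
|---|---|---|---|---|
| Stays, high or low use | yes | yes | yes | six months |
| Stops between T1 and T2 | yes | none, if not assessed after stopping | none, if not assessed after stopping | up to the stop |
| Stops before T1 | none, if not assessed after stopping | none, if not assessed after stopping | none, if not assessed after stopping | up to the stop |

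Usability is lost for stoppers, while use before the stop is still recorded.

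**Inputs.** The experimental arm has 120 participants (Intervention section). The plan gives no stop rate for device rejection and no expected SUS score, so there is no plan figure to reproduce for this endpoint. The 10% in the sample size section is a dropout allowance for the whole trial; I use it only as an anchor. All SUS scores and stop rates below are assumptions.

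**Usability at T2.** Let p be the share of the 120 who stop, c the mean SUS of continuers, and s the score stoppers would have given.

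- Observed mean = c
- Mean over all allocated = (1 − p)c + ps
- Overstatement = p(c − s)

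With c = 70 and p = 10% (12 of 120):

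- s = 40: (108×70 + 12×40)/120 = 67.0, overstated by 3.0
- s = 60: (108×70 + 12×60)/120 = 69.0, overstated by 1.0
- s = 70: 70.0, no bias

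Mean over all allocated, against an observed 70:

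| Stop share | s = 40 | s = 50 | s = 60 | s = 70 |
|---|---|---|---|---|
| 5% | 68.5 | 69.0 | 69.5 | 70.0 |
| 10% | 67.0 | 68.0 | 69.0 | 70.0 |
| 20% | 64.0 | 66.0 | 68.0 | 70.0 |
| 30% | 61.0 | 64.0 | 67.0 | 70.0 |

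**T1 against T2.** Suppose stops are split evenly around T1, s = 40 and p = 10%. The T1 mean is (108×70 + 6×40)/114 = 68.4 and the T2 mean is 70.0. Comparing all available scores shows a rise of 1.6 although nobody's score changed. Restricting the comparison to the 108 people with both scores gives 70 and 70, a change of zero.

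**Adherence.** Suppose continuers reach 80% of intended use and p = 10%.

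- Stoppers left out: 80%
- Stoppers counted as zero use: 0.9×80% = 72%, a ratio of 1/0.9 = 1.11
- Stoppers counted at half the continuers' use: 0.9×80% + 0.1×40% = 76%

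With stoppers at zero, the ratio runs from 1/0.95 = 1.05 at 5% stopping to 1/0.70 = 1.43 at 30%. If logs for all 120 are read over six months, with zero use after the stop, this error does not arise.

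**The case against.** The strongest reply is that nothing in the article restricts either endpoint to people still in the trial. It states no analysis set or denominator for them, and a separate analysis plan is promised. The stopping sentence sits in a risk section and does not say that assessments cease. This stands in part: silence on analysis sets is no fault here, and loss from follow-up is a reading, though the natural one of a sentence that ends the experiment. It does not remove the usability point, because the stated schedule has no occasion for rating at a stop.

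On adherence the reply largely succeeds. A reader might infer that adherence leaves out the non-adherent and is inflated. The documents do not support that. Technical data feed the endpoint, interactions are examined during the trial, low users who never ask to stop are measured, and late stoppers contribute T1 data. What remains is that the article does not say how time after stopping enters the frequency of use.

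A reader might also infer that the trial would report rising usability. That needs a comparison of T1 and T2 means from different sets of people, which the article does not plan. A conventional repeated-measures ANOVA over the two visits would use people with both scores and show no such artefact, although the level would still describe continuers only.

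Finally, the sizes rest on assumed scores and stop rates, and these are secondary endpoints with no stated threshold. Both points are fair and limit the weight of the concern.

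**Conclusion.** The point holds for usability in conditional form. If participants whose experiment is terminated are not assessed afterwards, those who reject the coach lack the ratings scheduled after they stop, and SUS and UEQ/UEQ+ summaries are likely to be overstated. At 10% stopping the SUS overstatement is about 1 to 3 points when stoppers would score 40 to 60 against 70. Over 5% to 30% stopping it is 0.5 to 9 points. It is zero if stoppers score the same. Upward bias is the plausible direction, given the stated reason for stopping, but the documents do not establish it.

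For adherence, overstatement follows only if stoppers are omitted or their time after stopping is not counted. The article says neither. The matter is worth correcting because the ratings cannot be collected afterwards, but it does not touch the primary outcome analysis.

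**What to change.** - Reconcile the Risk–benefit analysis section with Table 3: state whether participants who stop using the devices are still assessed, and when. The participant's right to stop is unchanged.
- Offer SUS and UEQ/UEQ+ once when a participant stops. Report these scores alongside the T1 and T2 results, not as T1 or T2 values. Carrying an exit score forward would impute a rating for months without use.
- Report adherence from system logs for all participants allocated to e-VITA over the planned six months, with zero use after the stop date. Keep the logs linkable to participants until this is done, since the Data management section describes the retained count as anonymous.
- Show T1-to-T2 change only in people measured at both visits.

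The cost is some wording, one added occasion for short questionnaires already in use, and a check on log linkage. Reported figures may be slightly less favourable. Some stoppers may decline the exit form, so the number who do should be given.

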#### Clinical frailty scale (CFS)

This descriptive scale divides the older participants into nine classes based on the information provided by them and their relatives: between 1 and 3, the patient is non-frail, pre-frail if 4, and he is frail from 5 to 9.

#### Montreal cognitive assessment (MoCA)

Montreal Cognitive Assessment (MoCA) serves as a validated cognitive test, which is recognized for its high sensitivity in the early detection of mild cognitive impairment (MCI). MoCA efficiently assesses various cognitive domains, including short-term memory, visuospatial abilities, executive functions, attention, concentration, working memory, language, and orientation to time and place. The final version of MoCA, accessible at www.mocatest.org, is a 1-page, 30-point test that can be administered in just 10 min. Specific details regarding the MoCA items are as follows: (1) Short-Term Memory Recall Task (5 points): involves two learning trials of five nouns and delayed recall after approximately 5 min; (2) Visuospatial Abilities (4 points): clock-drawing task (3 points), three-dimensional cube copy (1 point); (3) Executive Functions (4 points): alternation task adapted from the Trail Making B task (1 point), phonemic fluency task (1 point), two-item verbal abstraction task (2 points); (4) Attention, Concentration, and Working Memory (6 points): sustained attention task (target detection using tapping; 1 point), serial subtraction task (3 points), digits forward and backward (1 point each); (5) Language (8 points): three-item confrontation naming task with low-familiarity animals (lion, camel, and rhinoceros; 3 points), repetition of two syntactically complex sentences (2 points), phonemic fluency task; (6) Orientation to Time and Place (6 points): assessment of orientation across various dimensions. The comprehensive nature of MoCA allows for a thorough examination of cognitive abilities in a relatively short time frame.

#### Geriatric depression scale (GDS) 5-item version

This questionnaire assesses the current condition of the patient’s mood. For the screening required by our study, only the first five items of the scale can be used. The answers highlighted indicate the statements expected by a non-depressed subject.

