### Design/methodology

#### Recruitment

Patients are selected by the Neurology Operating Unit and Rehabilitation Medicine Operating Unit of IRCCS INRCA in the Ancona branch. After a reflection period of 2 weeks followed by reading the information letter and the consent form received by email, the participants who confirmed their wish to participate in the research by writing or orally will be invited by the investigator to consult a doctor during 3 months, preceding the start of the research. The doctor, volunteering to carry out the inclusion visits, will be the first to give the participants an information letter and two consent forms. Once the consent forms have undergone thorough proofreading and received signatures from both the participant and the doctor, the doctor will assess the participant’s eligibility for the research using an anamnesis Clinical Frailty Scale (CFS) (38), Montreal Cognitive Assessment (MOCA) (39), Geriatric Depression Scale (GDS) (40), and Short Physical Performance Battery (SPPB) (41). This comprehensive medical examination, conducted before the commencement of the experiment, will determine whether participants meet the inclusion criteria. Those who have signed the consent form but do not meet the inclusion criteria as confirmed by the doctor will be excluded from the research. The trial is scheduled to commence in May 2023 and is anticipated to conclude in December 2023.

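### The GDS < 9 entry criterion excludes nobody on the five-item GDS that the protocol describes

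*Protocol article*

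**What the plan says.** The inclusion criteria in the Participants section of the protocol article require GDS < 9, so a candidate is turned away on this criterion only at a score of 9 or more. The Recruitment section lists the GDS among the instruments with which the doctor decides eligibility at the inclusion visit.

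The instrument is described once, in a subsection headed "Geriatric depression scale (GDS) 5-item version". That subsection says: "For the screening required by our study, only the first five items of the scale can be used". On how answers are read it says only: "The answers highlighted indicate the statements expected by a non-depressed subject". It gives no points per item, no score range and no threshold.

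The GDS is also a secondary outcome, for psychological mood (Outcome measures). Table 3 schedules it at recruitment (R) and at the final evaluation (T2), and not at T0. Neither place names a version.

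**The concern.** The threshold and the instrument appear to belong to different versions of the scale. A cut-off of 9 cannot sort candidates on a five-item form if each item carries one point, because the total never gets that high.

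Four things depend on it:

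- **Population.** The trial is presented as one of healthy older adults. The GDS is the only mood instrument at recruitment, since the MoCA, SPPB and Clinical Frailty Scale cover cognition, physical function and frailty. If the GDS criterion does not operate, no mood threshold applies at entry.
- **Primary outcome and risk.** The EQ-5D-5L has an anxiety/depression dimension, so the range of mood enrolled bears on the baseline level and spread of the primary outcome. The Risk–benefit analysis section also names attachment and dependency as a hazard for vulnerable participants.
- **Consistency between centres.** Sites in four countries must apply this rule. A centre that gives a longer form and a centre that follows the five-item text would apply the same number to different scales.
- **Secondary outcome.** With no GDS at T0, the recruitment score has to serve as the baseline for change in mood. The screening form therefore also fixes the scale on which that change is measured.

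**Working it through.** There is no calculated figure in the plan to reproduce, because the cut-off is a stated rule. The check is whether the rule can ever reject a candidate.

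**Inputs**

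- Threshold: GDS < 9 (Participants, inclusion criteria).
- Number of items, k = 5 (heading and text of the GDS subsection).
- Points per item, p: not stated. I assume p = 1, because each answer is compared with the one expected of a non-depressed person. The assumption is varied below.

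**Formula**

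The maximum score is M = k × p. The scores that fail the criterion are the whole numbers from 9 to M, so their count is max(0, M − 8). The rule can reject someone only if k × p ≥ 9.

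**As written**

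M = 5 × 1 = 5, and max(0, 5 − 8) = 0 failing scores. Enumeration agrees. There are 2^5 = 32 response patterns, the highest total is 5, and none reaches 9. The criterion rejects 0 of 32 patterns, which is 0% of candidates whatever the distribution of mood among them.

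**How far the result depends on the assumption**

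The 15- and 30-item rows are illustrations; the article mentions neither length.

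| Items | Points per item | Maximum | Scores failing < 9 |
|---|---|---|---|
| 5 | 1 | 5 | none |
| 5 | 2 | 10 | 9 and 10 |
| 15 | 1 | 15 | 9 to 15 (7 values) |
| 30 | 1 | 30 | 9 to 30 (22 values) |

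At one point per item, at least nine items must be scored before the cut-off can reject anyone. With five items it would need at least two points per item (9 / 5 = 1.8, rounded up), and nothing in the article suggests that scoring.

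**Consequence for the secondary outcome**

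A five-item form at R leaves six possible baseline values, 0 to 5. If a longer form were given at T2, the two scores would be on different ranges and their difference would have no meaning as a change.

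**The case against.** The strongest reply is that the text is permissive. It says five items can be used, which may only allow a longer scale to be shortened. The threshold of 9 would then belong to the longer scale, and the screen would work wherever that scale is given. What stands is that the article does not prove which form centres will use, so the 0% figure applies to the five-item form. The reply does not remove the conflict. The subsection heading names the five-item version, and the sentence is about screening, which is exactly where the threshold applies. If shortening is optional, one cut-off governs two score ranges: it can reject on the long form and never on the short one.

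Other points on that side:

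- **The scoring is inferred.** This is true. The inference is reasonable, and only an unmentioned scoring of two or more points per item would overturn it.
- **A doctor examines each candidate, and acute or untreated medical problems are barred.** A doctor could turn away someone with evident untreated depression on that ground. That criterion sets no mood threshold, however, and does not repair the GDS one.
- **Randomisation protects the comparison.** This stands. A lax entry rule acts before allocation, on both arms alike, so it does not by itself bias the EQ-5D-5L comparison, and the sample-size calculation is untouched. No size has been shown for any effect on outcome variance.
- **The five items are tied to screening, so the T2 form is open, and no section says centres differ.** This is fair as far as it goes. A short range is not an error in itself, and divergence between centres is a risk rather than a documented fact. But Table 3 makes the screening score the only pre-intervention GDS, so the screening form cannot be separated from the outcome.

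**Conclusion.** The concern holds. The GDS threshold and the GDS version in the protocol article are incompatible. With the five-item form and one point per item, the maximum is 5 against a cut-off of 9, and the criterion rejects 0 of 32 response patterns. Under the permissive reading, the article still applies one threshold to two score ranges.

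The result rests on two assumptions: one point per item, and use of the five-item form that the article names. It concerns the GDS criterion and not every route by which a doctor might decline a candidate. It affects who is eligible, uniformity across centres and the interpretability of the GDS secondary outcome. It does not invalidate the randomised comparison or the sample size. This is a contradiction between two stated rules and not a detail left for the full protocol or analysis plan. It must be fixed, because an eligibility rule that cannot exclude anyone is not working as a rule.

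**What to change.** Reconcile the inclusion criteria with the GDS subsection. State one GDS version, its points per item and score range, and a threshold inside that range. There are two consistent routes:

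1. Name the longer version for which the cut-off of 9 was set, and correct the heading and text of the GDS subsection to match.
2. Keep the five-item version, and replace the cut-off with one that lies within 0 to 5.

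The article does not show which version or threshold was intended, so the choice belongs to the clinical team. Whichever route is taken, Table 3 and the Outcome measures section should name the version, and the same form should be used at R and T2 in every country so that change scores can be computed and pooled.

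The cost is protocol wording and, under the first route, a few more questionnaire items at visits that already take place.
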